# Comparison between the mesenteric fixation method (MEFIX) and conventional methods at preventing the occurrence of Petersen’s hernia: a study protocol for a multicenter randomized controlled trial

**DOI:** 10.1186/s13063-023-07841-9

**Published:** 2024-01-02

**Keywords:** Internal hernia, Minimally invasive surgery, Gastrectomy, Gastric neoplasm

## Abstract

**Background:**

Petersen’s hernia, which occurs after Billroth-II (B-II) or Roux-en-Y (REY) anastomosis, can be reduced by defect closure. This study aims to compare the incidence of bowel obstruction above Clavien–Dindo classification grade III due to Petersen’s hernia between the mesenteric fixation method and the conventional methods after laparoscopic or robotic gastrectomy.

**Methods:**

This study was designed as prospective, single-blind, non-inferiority randomized controlled multicenter trial in Korea. Patients with histologically diagnosed gastric cancer of clinical stages I, II, or III who underwent B-II or REY anastomosis after laparoscopic or robotic gastrectomy are enrolled in this study. Participants who meet the inclusion criteria are randomly assigned to two groups: a CLOSURE group that underwent conventional Petersen’s defect closure method and a MEFIX group that underwent the mesenteric fixation method. The primary endpoint is the number of patients who underwent surgery for bowel obstruction caused by Petersen’s hernia within 3 years after laparoscopic or robotic gastrectomy.

**Discussion:**

This trial is expected to provide high-level evidence showing that the MEFIX method can quickly and easily close Petersen’s defect without increased postoperative complications compared to the conventional method.

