### Sample size

Sample size calculation was based on an assumed proportion of Petersen’s hernia of approximately 1.15% for the conventional close method from our previously published papers [11]. The estimated difference in Petersen’s hernia proportions between close and MEFIX methods was assumed as 0.0% based on the previous similar study [11]. Thus, we set the inferiority threshold at 3% for clinical relevance. Therefore, if the proportion of Petersen’s hernia of the MEFIX method is less than 4.15%, the MEFIX method is not considered inferior to the conventional close method.

A sample size of 199 per arm is required for a proportion test with a one-sided significance level of 0.025 and power of 80% with no difference of hernia proportion between the two methods and a non-inferiority margin for the MEFIX method of 3% (non-inferiority limit = 0.03, treatment A (experimental) group = 0.0115, treatment B (control) group = 0.0115). Further, we decided to increase the sample size by 10% to cover possible dropouts. Consequently, 222 participants were included per group, and a total of 444 were needed. This calculation was performed as the PASS 13 (Power Analysis and Sample Size Software (2014). NCSS, LLC. Kaysville, UT, USA).

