### Statistical analysis

All outcomes are assessed using an intention-to-treat analysis that included all patients who were randomly assigned. However, patients who fall under “failure of major entry criteria,” such as those who are not treated at all or do not have available data after randomization, can be excluded from the ITT analysis. Per-protocol analysis also will be performed to evaluate the treatment effect under full compliance.

Demographic data and baseline characteristics of all randomized participants will be pooled. Data will be analyzed using R version 4.2.1 (R: a language and environment for statistical computing, R Foundation for Statistical Computing, Vienna, Austria). Continuous variables will be presented as mean and standard deviation or median and interquartile range. Categorical variables will be described as frequencies and percentages. We will analyze clinicopathological data and postoperative outcomes, including the primary and secondary endpoints, using the chi-square test, Fisher’s exact test, Student’s *t*-test (two samples), or Mann–Whitney *U*-test as appropriate methods based on the type of variables.

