To assess the non-inferiority of the MEFIX method compared with the conventional close method, a bilateral 95% confidence interval (CI) of the absolute difference in the Petersen’s hernia rate between the MEFIX group and the CLOSURE group will be estimated. The upper bound of this CI will be compared with the 3% of non-inferiority margin. The primary analysis of the primary endpoint (proportions of bowel obstruction caused by Petersen’s hernia) is performed based on chi-square test without adjustment for imbalance in baseline covariates. And we will calculate the hazard ratio of MEFIX group compared to CLOSURE group by Cox proportional hazard analysis with adjusting covariates. Additionally, secondary endpoints will be analyzed with equivalent test, and dichotomous variables will be compared between the two groups using adjusted and unadjusted hazard ratios and 95% CI by Cox proportional hazard analysis. Unadjusted analyses of time to event for primary and secondary endpoints will be presented using Kaplan-Meier curves and analyzed for non-inferiority of median time to event using the log-rank test. Candidate variables will be subsequently incorporated into a logistic regression analysis. We will express multivariate comparisons as hazard ratios with corresponding 95% CI. For all analyses, *p* < 0.05 will be considered significant statistically. There will be no imputation used to handle missing data during the analysis.

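### The expected conclusion of no increase in postoperative complications has no limit to be judged against, and a non-significant difference cannot support it

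*Protocol article*

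**What the plan says.** The Discussion paragraph of the abstract states the expected result: MEFIX closes the defect quickly and easily, "without increased postoperative complications compared to the conventional method". The Conclusions add that positive results could mean fewer complications. Short-term complications within 30 days, small bowel obstruction within 30 days and bleeding during the mesenteric suture are listed as secondary outcomes. No expected rate is given for any of them.

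The Statistical analysis section says several things about how such outcomes are handled:

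- "We will analyze clinicopathological data and postoperative outcomes, including the primary and secondary endpoints, using the chi-square test", with Fisher's exact, t or Mann–Whitney tests as alternatives.
- "secondary endpoints will be analyzed with equivalent test, and dichotomous variables will be compared between the two groups using adjusted and unadjusted hazard ratios", with 95% confidence intervals.
- Time to event for primary and secondary endpoints is "analyzed for non-inferiority of median time to event using the log-rank test".
- "For all analyses, *p* < 0.05 will be considered significant statistically".

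The only decision rule based on a confidence bound concerns the hernia rate: "The upper bound of this CI will be compared with the 3% of non-inferiority margin".

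**The concern.** To say that a method works without more complications is to say it is no worse, and that needs a bound on the excess that the data rule out. The article applies this logic to the hernia rate, where it fixes a margin and compares an upper confidence bound with it. For complications it states the same kind of conclusion but supplies no comparable rule.

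None of the listed methods fills the gap. Chi-square and Fisher tests look for a difference, and failing to find one does not show that there is none. If the equivalent test is an equivalence test, it cannot be run without limits. If it only means a test of the same kind, it is again a test of difference. The hazard ratios come with intervals, but nothing says what an interval must exclude. The log-rank non-inferiority wording carries no margin.

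At stake is the safety part of the trial's message. A reader of the final report could take a non-significant comparison as confirmation of the sentence in the abstract, although the trial was sized for a hernia rate of 1.15% and not for complications.

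**Working it through.** **Inputs from the article.** The Sample size section gives hernia rates of 0.0115 in both arms, a margin of 0.03, one-sided 0.025, power 80%, 199 per arm, and 222 per arm after a 10% dropout allowance. The significance level for other analyses is 0.05.

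**Inputs assumed.** The 0.05 level is two-sided for tests of difference. CLOSURE complication rates run from 1% to 20%. A 5-point increase is an illustration only.

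**1. The article's own figure.** "A sample size of 199 per arm is required for a proportion test with a one-sided significance level of 0.025 and power of 80"%. With unpooled variance,

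n = (1.96 + 0.8416)² × 2 × 0.0115 × 0.9885 / 0.03² = 7.849 × 0.022736 / 0.0009 = 198.3, so 199.

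Then 199 / 0.9 = 221.1, so 222. Both figures reproduce. They concern the hernia endpoint only.

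**2. Chance of missing a 5-point increase.** By normal approximation, at 10% versus 15% with 199 per arm:

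- Standard error under no difference: √(2 × 0.125 × 0.875 / 199) = 0.03316.
- Standard error under the alternative: √((0.09 + 0.1275) / 199) = 0.03306.
- z = (0.05 − 1.96 × 0.03316) / 0.03306 = −0.45, so power is about 0.325 and the miss rate about 68%.

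Exact binomial enumeration of the uncorrected chi-square test gives these miss rates (1 minus the chance of significance with MEFIX worse):

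| Assumed CLOSURE rate | 199 per arm | 222 per arm |
|---|---|---|
| 1% | 18% | 13% |
| 2% | 30% | 25% |
| 3% | 40% | 35% |
| 5% | 52% | 48% |
| 10% | 68% | 64% |
| 15% | 74% | 72% |
| 20% | 78% | 76% |

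Missing a 5-point increase becomes more likely than not once the CLOSURE rate passes about 4.5% (199 per arm) or 5.5% (222 per arm).

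**3. Larger increases.** At 199 per arm and CLOSURE rates of 10%, 15% and 20%, the miss rate is 41%, 51% and 58% for 7.5 points, and 19%, 29% and 36% for 10 points.

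**4. What a null result leaves open.** With equal observed rates p, the 95% half-width for the risk difference is 1.96 × √(2p(1 − p) / 199). That is 5.9 points at 10%, 7.0 at 15% and 7.9 at 20%.

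**5. Margin that could be met with 80% power** if the true rates are equal: 2.8 × √(2p(1 − p) / 199).

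- p = 10%: 2.8 × 0.0301 = 8.4 points.
- p = 20%: 2.8 × 0.0401 = 11.2 points.

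A margin equal to the half-width in step 4 would be met only about half the time.

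**The case against.** - **The abstract sentence is an expectation, not a decision rule.** This stands. A reader might infer that the plan commits to declaring no increase whenever p > 0.05. No section says so. What can be said is that nothing in the stated analysis could support the sentence.
- **Intervals are planned.** This stands too. It would be wrong to say that complications rest on p-values alone: hazard ratios with 95% confidence intervals are foreseen, and an equivalent test is named. What is missing is any limit against which a bound is judged.
- **The phrase may include the primary endpoint, which has a margin.** Obstruction from Petersen's hernia is a postoperative complication, so this is partly fair. But the phrase speaks of postoperative complications in general, the article lists 30-day complications as a separate outcome, and the Conclusions name complications apart from hernia prevention. The 3% rule does not reach those.
- **Limits for secondary endpoints are often left to the full protocol or analysis plan.** True, and an absent margin alone would be no finding. Here, however, the article sets out both the secondary analyses and the conclusion, and the two do not fit together.
- **The size depends on chosen rates, and low power for secondary outcomes is common.** This stands as a limit on the figures. A reader might infer that the trial would usually miss any important rise. That is not supported: at CLOSURE rates of 1% to 3% a 5-point rise would usually be found, and so would a 10-point rise at rates of 10% to 20%. In addition, 30-day outcomes should mostly be observed before long-term dropout, so 222 per arm may be the fairer figure. It changes little at rates of 10% or more.

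**Conclusion.** The point holds in this form: the article expects a no-worse-than conclusion on complications, and its stated methods contain no limit by which that conclusion could be reached. This does not depend on any assumed rate.

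The size does. If the CLOSURE complication rate is between 5% and 20%, a true 5-point increase would be missed with probability 52% to 78% at 199 per arm (48% to 76% at 222). If the rate is 1% to 3%, the probability is 18% to 40% (13% to 35% at 222). These figures assume a two-sided 5% chi-square test and 5 points as an illustration.

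The primary non-inferiority analysis is not affected.

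**What to change.** In the Statistical analysis section, replace the undefined equivalent test for 30-day complications, 30-day small bowel obstruction and suture bleeding with the MEFIX minus CLOSURE risk difference and its two-sided 95% confidence interval. State that p > 0.05 is not evidence of no increase, and that the upper bound is reported as the excess not excluded. Allow a conclusion of no increase only if that bound lies below a margin that the sponsor has fixed and justified before the analysis. If the full protocol or analysis plan already holds such limits, cite them.

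Reword the abstract to say that the trial will estimate the difference in postoperative complications with its 95% confidence interval, and bring the Conclusions into line.

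The change takes a few sentences and uses data already being collected, with no extra patients. The price is a more modest safety claim: at 199 per arm and rates of 10% to 20%, only margins of about 8 to 11 points could be met with 80% power. If margins that wide are not acceptable as showing no increase, the estimate with its interval should stand alone.

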**Trial registration:**

ClinicalTrials.gov NCT05105360. Registered on November 3, 2021.

**Supplementary Information:**

The online version contains supplementary material available at 10.1186/s13063-023-07841-9.

## Background

Petersen’s hernia was first described in 1900 by Walther Petersen, a German surgeon, following the appearance of an internal hernia after gastrectomy and gastrojejunostomy (GJ) [1]. The space between the mesentery of the small intestine and the transverse colon after the gastrojejunal or esophageal-jejunal anastomosis is called “Petersen’s defect.” In Petersen’s hernia, the mesentery rotates and twists; therefore, an emergency event may occur in which the entire small intestine is necrotic due to impaired blood circulation.

After laparoscopy-assisted distal gastrectomy was first performed in 1994, it has become the standard surgery for early gastric cancer, as reported by Kitano et al. [2]. It is minimally invasive compared with open surgery, which reduces the risk of postoperative adhesions, recovery time of bowel movements, hospital stay, and postoperative pain. However, due to relatively fewer adhesions, the incidence of internal hernias is higher in laparoscopic surgery than with open surgery, and the incidence of Petersen’s hernia after laparoscopic REY gastrojejunostomy is reported to be 1.7–9.7% [3–8]. The anti-adhesive agent, which has been widely used recently, is also thought to be one of the reasons for the increased incidence of internal herniation [9]. According to Blockhuys et al., the incidence of internal hernias decreases when Petersen’s defect closes [10]. Many surgeons also believe that closure of the mesenteric defect with nonabsorbable sutures prevents Petersen’s hernia.

As the method of Petersen’s defect closure, the mesentery of the small intestine and transverse colon is closed with a suture. However, in patients with thin mesentery, tearing is common, and there is a high risk of damage to the small arterioles, which can lead to bleeding and ischemia of the small intestine. Additionally, the narrow surgical field and the close proximity of the surgical instruments can make the suturing of the mesentery challenging. The MEFIX technique is a recently developed approach for which there have yet to be any comparative studies on operative time with the conventional defect closure method. In our previous retrospective study, we exclusively compared this technique, and the time taken to close Petersen’s defect was 3.7 ± 1.1 min for the MEFIX method and 7.5 ± 1.5 min for the conventional method, respectively (*p* < 0.001) [11]. It suggests that a more efficient technique could be necessary for closure of the Petersen’s defect.

In this study, we propose a novel mesenteric fixation method (MEFIX) to prevent Petersen’s hernia, in which a portion of the mesentery of the small intestine is fixed to the mesentery of the transverse colon. It prevents Petersen’s hernia by preventing total herniation of the mesentery of the small intestine even if partial internal hernia is possible by creating the effect of adhesion of the small intestine to the surgical site during laparotomy [11] (Fig. 1).

**Fig. 1 Fig1:**
[figure not shown]
The concept of conventional closure (**A**–**D**) and mesentery fixation methods (**E**–**H**). This method allowed partial herniation of the bowel, but it prevented of total SB herniation and necrosis. MEFIX, mesentery fixation; SB, small bowel

## Methods

The trial protocol is identified as version 2.0 of 27 December 2022. This protocol has been drafted in accordance with the Standard Protocol Items: Recommendations for Interventional Trials (SPIRIT). The SPIRIT checklists can be found as Additional file 1.

### Objectives

This study aims to compare the incidence of intestinal obstruction above the Clavien-Dindo classification grade III due to Petersen’s hernia between the MEFIX method and conventional closure methods after minimally invasive surgery such as laparoscopic or robotic gastrectomy.

### Study design and participants

This study was designed as prospective, single-blind, non-inferiority randomized controlled multicenter trial in Korea. We enroll patients with histologically diagnosed gastric cancer of clinical stages I, II, or III who underwent B-II or REY anastomosis after laparoscopic or robotic gastrectomy. Patients who meet the inclusion criteria are randomly assigned to two groups: a CLOSURE group that underwent conventional Petersen’s defect closure and a MEFIX group that underwent the mesenteric fixation method. Computed tomography (CT) will be performed every 6 months for the first 3 years after surgery and every 1 year for the next 2 years. A history of outpatient or emergency department visits for symptoms of internal hernia, such as vomiting and abdominal pain, or emergency surgery for internal hernia will be examined (Fig. 2 and Table 1).

**Fig. 2 Fig2:**
[figure not shown]
Flow chart of study protocol

**Table 1 Tab1:** Timetable of the study period

	Study period										
	Enrolment	Allocation	Post-allocation (months)								Close-out
Time point		Surgery	6	12	18	24	30	36	48	60	5 years after surgery
Enrolment											
Eligibility screen	x										
Informed consent	x										
Allocation		x									
Interventions											
CLOSURE		x									
MEFIX		x									
Assessment											
Evaluation of Petersen’s hernia			x	x	x	x	x	x	x	x	x

### Eligibility criteria

#### A) Inclusion criteria

Histologically confirmed primary gastric adenocarcinomaNo evidence of other distant metastasisUnderwent laparoscopic total or distal gastrectomyUnderwent robotic total or distal gastrectomyReconstructed by B-II or REY procedureAged 20 or olderPatients with appropriate activity conditions: 0 or 1 on the Eastern Cooperative Oncology Group (ECOG) scalePatients who had not previously received abdominal chemotherapy or radiation treatmentPatients who signed the consent form

#### B) Exclusion criteria

Active double cancer (i.e., synchronous and metachronous double cancer within 5 disease-free years) and carcinoma in situ (i.e., lesions suggestive of intraepithelial or intramucosal cancer)Gastric cancer recurrenceA history of abdominal surgery, with the exception of laparoscopic appendectomy, gallbladder resection, laparoscopic gynecologic surgery for benign neoplasms, and cesarean sectionPatients in whom other organs must be coordinated during the preoperative examination (however, laparoscopic cholecystectomy is included in the selection criteria due to gallbladder polyps and gallbladder disease)Pregnant or lactating womenDiagnosed with mental illness in the medical recordsPatients taking whole-body corticosteroids, including herbal medicinesAn uncontrolled history of angina or myocardial infarction within 6 months before the study periodUncontrolled hypertensionPatients suffering from a severe respiratory disease requiring continuous oxygen therapy

#### C) Elimination criteria

If a patient has expressed an intention to discontinue participation in the study before or after the study has begunParticipants who did not undergo an appropriate operation (laparoscopic or robotic distal gastrectomy with B-II or REY anastomosis) or do not have available outcome data

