### Randomization

Patients are randomly assigned in a 1:1 ratio to the MEFIX or CLOSURE group. Allocation is conducted by computer-generated permuted random blocks (size 4) stratified by 12 hospitals. Block randomization is performed by an independent biomedical statistician using R software. A principal investigator (PI) retains the random assignment tables from each hospital. When eligible patients are recruited from each hospital, the clinical research coordinator (CRC) at the PI’s institution is notified. The CRC then confirms the randomization result on the day prior to the surgery and subsequently informs the respective institution.

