#### A) Operative methods for Petersen’s defect closure (CLOSURE group)

The Petersen’s defect, which occurs between the mesentery of the jejunum and transverse colon, is sutured with a nonabsorbable thread after a gastrojejunal or esophageal-jejunal anastomosis. First, a traction suture is performed between the jejunum and transverse colon, and Petersen’s defect is closed continuously using a nonabsorbable barbed suture V-Loc™ 3-0 (Medtronic VR, Minneapolis, MN, USA). Because leaving the tip of the barbed suture can cause bowel obstruction, backward suture with the V-Loc 3-0 was performed two to three times at the last suturing step. Subsequently, the tip is cut short after anchoring (Fig. 3).

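### The elimination criteria, read literally, remove eligible total-gastrectomy patients after randomisation and name no analysis set, and the intention-to-treat definition contradicts itself

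*Protocol article*

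**What the plan says.** All places are in the protocol article.

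- **Eligibility criteria, A) Inclusion criteria:** total and distal gastrectomy both qualify, listed once for laparoscopic and once for robotic surgery.
- **Operative methods, CLOSURE group:** the defect "is sutured with a nonabsorbable thread after a gastrojejunal or esophageal-jejunal anastomosis". The technique therefore covers the oesophageal-jejunal anastomosis as well as the gastrojejunal one.
- **Eligibility criteria, C) Elimination criteria:** participants are eliminated if they "did not undergo an appropriate operation (laparoscopic or robotic distal gastrectomy with B-II or REY anastomosis) or do not have available outcome data". Anyone who says they wish to stop, before or after the study starts, is also eliminated. No analysis set is named.
- **Randomization:** "The CRC then confirms the randomization result on the day prior to the surgery". Elimination based on the operation performed, on missing outcome or on later withdrawal therefore comes after allocation.
- **Statistical analysis:** "All outcomes are assessed using an intention-to-treat analysis that included all patients who were randomly assigned". The next sentence makes an exception for patients it regards as major failures at entry: "such as those who are not treated at all or do not have available data after randomization, can be excluded from the ITT analysis". The section then adds: "Per-protocol analysis also will be performed to evaluate the treatment effect under full compliance". On missing values: "There will be no imputation used to handle missing data during the analysis".

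**The concern.** There are two linked defects.

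First, the list of appropriate operations in the elimination criteria is narrower than the list of eligible operations. A patient can meet every inclusion criterion, be randomised, receive the allocated technique, be followed for 3 years, and still meet the wording for elimination.

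Second, it is unclear who is in the primary analysis. The elimination criteria do not say whether they act on the ITT set, the per-protocol set or both. The ITT definition promises everyone randomised and then permits exclusions. Having no data after randomisation is not a failure of an entry criterion, yet it is given as an example of one. The permission is also discretionary (patients can be excluded), so two analysts could build different sets from the same data.

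The trial is single-blind, and the Data collection section says the data collectors are not blinded. The principal investigator keeps the assignment tables (Randomization) and also assesses the primary outcome (Assessment of outcomes). Post-randomisation exclusions should not be left to judgement in that setting. Very few events are expected, so the result depends on which patients are counted.

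**Working it through.** **1. The texts side by side**

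| Patient | Inclusion criteria | Elimination criteria | ITT, first sentence | ITT exception |
|---|---|---|---|---|
| Total gastrectomy, treated, followed | eligible | eliminated (only distal is named) | included | not covered |
| Treated, then withdraws | eligible | eliminated | included | not covered if some data exist |
| No outcome data | eligible | eliminated | included | may be excluded |
| Not treated at all | not decided by this list | eliminated (no appropriate operation) | included | may be excluded |

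For the first two rows, the elimination criteria go beyond anything the ITT exception allows. For the last two, the elimination criteria and the exception agree with each other, and both conflict with the ITT definition's first sentence.

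**2. The protocol's own sample size**

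Inputs (Sample size): 1.15% in both arms, margin 0.03, one-sided 0.025, power 80%, 10% dropout.

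n = (1.96 + 0.8416)² × 2 × 0.0115 × 0.9885 / 0.03² = 198.3, so 199 per arm. Then 199 / 0.90 = 221.1, so 222 per arm and 444 in total. Both stated figures reproduce.

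**3. Power if the elimination wording is applied literally**

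The total-gastrectomy share is not in the document; 10–25% is an assumption.

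Power = Φ(0.03 / √(2 × 0.0115 × 0.9885 / n) − 1.96)

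- After 10% dropout: 222 × 0.90 = 199.8; Φ(2.812 − 1.96) = 0.80.
- Share 10%: 199.8 × 0.90 ≈ 180; Φ(2.669 − 1.96) = 0.76.
- Share 25%: 199.8 × 0.75 ≈ 150; Φ(2.437 − 1.96) = 0.68.

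**4. Sensitivity to single events**

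Expected events per arm: 199 × 0.0115 = 2.3.

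For illustration, take the Wald upper 95% bound of the difference, p₁ − p₀ + 1.96 × √(p₁(1 − p₁)/n₁ + p₀(1 − p₀)/n₀), with 2 CLOSURE events among 199:

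- 4 MEFIX events among 199: 0.0101 + 1.96 × 0.0122 = 0.034. Above 3%, so non-inferiority is not shown.
- 3 MEFIX events among 199: 0.0050 + 1.96 × 0.0112 = 0.027. Below 3%, so non-inferior.
- Start from 4 and eliminate one MEFIX patient who had an event, leaving 3 among 198: 0.0051 + 1.96 × 0.0112 = 0.027. The conclusion reverses.

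The effect can also run the other way. With 3 against 2 events but only 150 per arm, the bound is 0.0067 + 1.96 × 0.0148 = 0.036, and non-inferiority is no longer shown.

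**The case against.** The strongest reply is that the distal-only wording is a drafting slip. The Abstract, Study design and participants, and Primary outcome sections speak of laparoscopic or robotic gastrectomy without restriction. The inclusion criteria name total gastrectomy twice, and only one parenthesis omits it. That is probably right about intent. But the parenthesis sits in an operative rule for a trial across 12 hospitals, and it still conflicts with the inclusion criteria.

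Several stronger readings are tempting, and the document does not support them:

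- **Total-gastrectomy patients vanish from the ITT result.** This does not follow. The elimination criteria name no analysis set, and the ITT exception does not mention type of gastrectomy. The defect is that the text leaves the matter open.
- **Dropping patients without outcome data contradicts the analysis section as a whole.** It contradicts only the first ITT sentence. The next one says that those who "do not have available data after randomization, can be excluded from the ITT analysis", so on this point the two sections agree. The contradiction lies within the Statistical analysis section.
- **Patients with events are always kept while event-free patients are lost.** The criteria would also eliminate a total-gastrectomy patient who had a hernia, and a patient who withdrew after one. No passage classes a patient who died as lacking outcome data. The direction of any bias cannot be read from the text.
- **The trial is unblinded.** It is stated to be single-blind; only the data collectors are said to be unblinded.
- **The sample size is wrong.** It is not; 199 and 222 reproduce.

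It is also fair to say that partial follow-up is not ignored. Kaplan–Meier curves, a log-rank test and Cox models are already planned for the primary endpoint. The decision, however, rests on a simple difference in proportions, and that is where the composition of the set matters.

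**Conclusion.** The point holds as an inconsistency of wording with consequences for the primary analysis. The inclusion and elimination criteria disagree on total gastrectomy; the elimination criteria do not say which set they govern; and the ITT definition contradicts itself.

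The loss of power to 76–68% is conditional on three things: a total-gastrectomy share of 10–25%, which is assumed; literal application of the elimination wording to the analysed set; and the protocol's normal-approximation formula. The reversal by one event is an illustration with chosen counts close to the expected 2.3 per arm, not a forecast. The textual conflict needs none of these assumptions. It should be settled before the single final analysis planned once the last participant reaches 3 years.

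**What to change.** 1. Reconcile the elimination criteria with the inclusion criteria, so that the appropriate operation reads as total or distal gastrectomy with either reconstruction.
2. State that the elimination criteria define the per-protocol set only.
3. Define ITT as all randomised patients, analysed as allocated, using data up to withdrawal. Delete the exception that treats missing data as a failure of entry criteria.
4. State that a patient who dies without surgery for Petersen's hernia is a known non-event for the 3-year primary endpoint.
5. Do not carry patients lost to follow-up forward as non-events. That would be single imputation, which the plan rules out, and by adding unobserved non-events it would favour non-inferiority. Use their partial follow-up in a supportive difference in 3-year cumulative incidence, with death as a competing event.

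Items 1 to 4 are wording changes. Item 5 costs one extra analysis on data already collected. The stated sample size does not change.
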